#### 2.9.2. Secondary outcome.

The secondary outcomes at 3 months will be used to assess changes in cardiopulmonary endurance by 1 MET (peak oxygen consumption rate [VO_2_] 3.5 mL/kg/minutes), VO_2_ max, and VO_2_ at the anabolic threshold. At 6 and 12 months, improvement and maintenance of cardiorespiratory endurance by 1 MET (peak VO_2_ 3.5 mL/kg/minutes), VO_2_ max, and VO_2_ at anabolic threshold will be assessed.

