### 2.11. Statistical analysis

The analysis of this study was performed using an intention-to-treat and per-protocol method. CR participation, defined as the number of sessions completed, will be analyzed as a continuous variable using the student *t* test or Mann–Whitney *U* test, based on the normal distribution of the data. CR completion and categorical variables will be analyzed using chi-square or Fisher’s exact test. Missing data will be replaced using the last observation carried forward or the mean value. In the case of more than 20% of dropouts, missing data in the intent-to-treat analysis will be replaced using multiple imputations. The intention-to-treat population will include all enrolled participants, and the per-protocol analysis will include patients who have completed the 3-month evaluation.

Changes in secondary outcomes over time for the CPET, KASI, EuroQol 5 dimensions, and patient health questionnaire will be analyzed using paired t-tests with comparisons from baseline. Analyses will be conducted for each of the intervention, control, CR completion, and non-completed groups. For non-normal distributions, the Wilcoxon signed-rank test will be used.

Statistical significance will be set at *P* < .05, and SPSS version 20 (IBM SPSS Statistics, New York, NY) will be used for the statistical analysis.

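### The planned CPET test uses neither the 1-MET size nor the 3-month value, so a significant result can be misread as a 1-MET improvement or as maintenance

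*Protocol article*

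**What the plan says.** Section 2.9.2 gives the cardiorespiratory outcome a size and a time course. For month 3: "The secondary outcomes at 3 months will be used to assess changes in cardiopulmonary endurance by 1 MET", with 1 MET equated to 3.5 mL/kg/min of peak VO2. For the later visits: "At 6 and 12 months, improvement and maintenance of cardiorespiratory endurance by 1 MET (peak VO_2_ 3.5 mL/kg/minutes"). VO2 max and VO2 at the threshold are listed beside the 1-MET item.

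Section 2.11 states how these data are analysed. One sentence groups the measures, CPET among them: "Changes in secondary outcomes over time for the CPET, KASI, EuroQol 5 dimensions, and patient health questionnaire". It gives all of them a single method, in that they "will be analyzed using paired t-tests with comparisons from baseline". The fallback keeps the same structure: "For non-normal distributions, the Wilcoxon signed-rank test will be used". The tests are run group by group: "Analyses will be conducted for each of the intervention, control, CR completion, and non-completed groups". A general sentence covers yes/no variables, "CR completion and categorical variables will be analyzed using chi-square or Fisher’s exact test", but names no CPET variable. The significance rule is "Statistical significance will be set at *P* < .05".

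Section 2.8.1 and Table 1 schedule CPET at baseline and at 3, 6 and 12 months.

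**The concern.** The outcome asks two things: whether endurance rose by 1 MET, and whether the rise was kept after the programme ended. The stated test asks something else: whether the mean change from baseline differs from zero within a group. The value 3.5 mL/kg/min plays no part in it. The reference is always baseline, so a gain fully kept from month 3 and a gain partly lost can both give a significant result.

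This is not just silence in a condensed article. Section 2.11 names CPET and fixes its test and its reference point, and that rule does not answer the outcome in section 2.9.2. At stake is the reading of the long-term result: significance at month 12 could be taken as maintenance of a 1-MET gain when the data show something smaller.

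**Working it through.** **The plan's own figure.** The article gives no design figure for the 1-MET outcome. Its only one is 22 per group for completion of 55.4% versus 15.4% at power 0.8 (section 2.5). Two-sided 5%, pooled variance, mean proportion 0.354:

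n = [1.960 × √(2 × 0.354 × 0.646) + 0.842 × √(0.554 × 0.446 + 0.154 × 0.846)]² / 0.40² = (1.326 + 0.517)² / 0.16 ≈ 21.2, rounded up to 22.

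This reproduces, and the present point does not touch it.

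**Inputs for the check.**
- n = 24 per arm (section 2.5).
- Alpha 0.05 (section 2.11), taken as two-sided because the article does not state sidedness.
- Threshold 3.5 mL/kg/min (section 2.9.2).
- SD of change in peak VO2: not in the document. Assumed 3, 4 and 5 mL/kg/min.
- A gain of 3.5 at month 3 that halves to 1.75 at month 12: an illustration, not a figure from the document.

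**Step 1: smallest mean change that is significant against zero.** t(0.975, 23) × SD / √24 = 2.069 × SD / 4.899.

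**Step 2: probability that the test against baseline is significant when the true mean change is 1.75.** Noncentral t with 23 degrees of freedom and noncentrality 1.75 × √24 / SD = 2.86, 2.14 and 1.71.

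**Step 3: share of patients at or above 1 MET when the mean is 1.75.** With normal changes, 1 − Φ((3.5 − 1.75) / SD).

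| Assumed SD | Smallest significant mean change | In MET (÷ 3.5) | P(significant), true mean 1.75 | Share ≥ 1 MET, mean 1.75 |
|---|---|---|---|---|
| 3 | 1.27 | 0.36 | 0.78 | 28% |
| 4 | 1.69 | 0.48 | 0.54 | 33% |
| 5 | 2.11 | 0.60 | 0.38 | 36% |

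**Comparator for the last column.** If the mean gain of 3.5 is fully kept, the share is 1 − Φ(0) = 50% at every SD. The 28% to 36% must be read against 50%, not against 100%.

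**Sensitivity.** At n = 22 the smallest significant changes are 1.33, 1.77 and 2.22. In a subgroup of 12 they are 1.91, 2.54 and 3.18 (0.54 to 0.91 MET), still below 1 MET. At SD 2 and n = 24, significance starts at 0.84 and the half-lost gain is significant with probability 0.98.

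**Step 4: would a significance test from month 3 settle maintenance?** Not on its own. If the change from month 3 to month 12 has the same SDs, a paired test at n = 24 detects a loss of 1.75 with the same probability, 0.78 to 0.38. It misses that loss 22% to 62% of the time, so a non-significant change from month 3 does not show maintenance.

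**Step 5: effect of the missing-data rule.** Section 2.11 allows last observation carried forward, with multiple imputation reserved for dropout above 20%. A patient tested at month 3 but not later would receive the month-3 value, so the change from month 3 is zero by construction and the gain counts as kept.

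**The case against.** The strongest reply is that 1 MET is a scale or a benchmark of clinical relevance and not a cut-off. The abstract gives the outcome as VO2 max and VO2 at the threshold, both continuous, and the Table 1 footnote names no responder variable. On that reading a paired test of change is a natural analysis. Being still above baseline at 6 and 12 months is also a possible meaning of maintenance, and section 2.9.1 uses the baseline reference for the patient-reported outcomes. An operational definition of either term could sit in an analysis plan that is not shown.

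Part of this stands. The wording allows more than one reading, and a baseline reference is not wrong in itself. But even as a benchmark, 1 MET is the size that section 2.9.2 attaches to the outcome, and no stated analysis uses it. A later definition would have to add to the CPET rule already given or depart from it.

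A reader might infer that the trial will declare success on a half-lost gain. The documents do not support that. They define no success rule for this outcome, and the probability depends on an SD they do not give: at SD 5 the half-lost gain is usually not significant. A reader might also infer that 1-MET improvement cannot be obtained at all. That too goes further than the text. The mean change and its confidence interval could be set beside 3.5, and a yes/no variable, once defined, would fall under the general chi-square/Fisher sentence. Neither route is stated, and neither measures loss after month 3.

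Whether section 2.11 should compare the arms on the continuous CPET measures is a separate question.

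**Conclusion.** The point holds as a mismatch between a stated outcome and its stated test. A significant change from baseline establishes neither a 1-MET gain nor its maintenance. With 24 per arm and an assumed SD of 3 to 5 mL/kg/min, significance begins at 0.36 to 0.60 MET. The chance that a half-lost gain is still significant runs from 0.78 down to 0.38. These sizes rest on the assumed SD, on normal changes and on a hypothetical halving; the mismatch itself does not. It affects one secondary outcome and leaves the attendance outcomes and the sample size untouched. It should be corrected, but it does not threaten the trial's main question.

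**What to change.** Keep the continuous change analysis and add the following to sections 2.9.2 and 2.11:

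1. A per-patient indicator at 3, 6 and 12 months: peak VO2 at least 3.5 mL/kg/min above baseline. Compare it by arm with the chi-square or Fisher test already planned.
2. The mean change from month 3 to months 6 and 12, with a 95% confidence interval.
3. A statement that maintenance is judged on that estimate and on the proportion still at least 1 MET above baseline. It is not inferred from a significant change from baseline or from a non-significant change from month 3.
4. No last observation carried forward for this analysis, because it sets loss after month 3 to zero for dropouts. Multiple imputation, already named in section 2.11, is one alternative.

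The cost is added wording and analysis. CPET is already collected at all four time points, so no visit, patient or measurement is added. There are two downsides. The responder comparison has low power: 24 per arm gives power 0.85 for a difference as large as 55.4% versus 15.4%, and much less for the smaller differences that may be expected here. The maintenance result may also look less favourable than one based on change from baseline.

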#### 2.9.3. Benefits and risks for participants.

##### 2.9.3.1. Benefits.

Participation in this study does not guarantee medical benefits. However, incentives motivate people to increase their participation in CR exercises, and participants can improve their recovery from the disease by actively participating in the program.

##### 2.9.3.2. Risks and discomforts.

Regarding participation, a difference exists only in the provision of incentives. However, there are no additional risks or discomfort for participating in the study because all procedures are to be performed in accordance with standard practice procedures.

### 2.10. Monitoring

#### 2.10.1. Standard medical procedures and research procedures.

The interventions used in this study will differ in the provision of transportation expenses between the control and experimental groups; otherwise, there will be no difference in treatment compared to conventional treatments. Exercise stress testing, cardiovascular imaging, labs, and echocardiography are standard practice procedures in which the cost of the test will be supported by research funds.

#### 2.10.2. Continuous safety monitoring and data safety monitoring plans.

The principal investigator, project manager, and monitoring agent from the Korean Center for Disease Control and Prevention will conduct monitoring every 6 months. If a severe adverse reaction occurs during the study, the event will be immediately reported to the Institutional Review Board (IRB). If a minor adverse reaction occurs, the event will be reported to the IRB after monitoring is performed by the principal investigator and project manager.

Interim analyses and reports will be reported once a year to the IRB, and if modifications are required for the study protocol, permission will be granted by the IRB.

Auditing will be performed by the IRB once a year or when severe adverse events, unexpected events, or significant protocol deviations are reported, and a decision on whether to terminate the study early will be taken.

#### 2.10.3. Data-monitoring committee (DMC), safety monitoring methods, and cycles.

The DMC will be comprised of several members of the IRB, including at least 1 outside the hospital. When a participant receives an explanation and consent form, the principal investigator will explain the reporting system of the adverse reactions and instruct the participant to immediately inform the researcher if an adverse reaction occurs. The presence or absence of adverse reactions will be confirmed upon completion of the assessment. DMC will analyze the study accruals and report adverse reactions every 4 months or when severe adverse events or unexpected events are reported.

#### 2.10.4. Adverse drug reaction report, noncompliance with studies, and unexpected event report.

Severe adverse events, noncompliance with major studies, or unexpected problems will be reported to the IRB by monitoring personnel within 15 working days from the date of recognition by the researcher. If the event is death or life-threatening, it will be reported to the IRB within 7 days.

### 2.11. Statistical analysis

The analysis of this study was performed using an intention-to-treat and per-protocol method. CR participation, defined as the number of sessions completed, will be analyzed as a continuous variable using the student *t* test or Mann–Whitney *U* test, based on the normal distribution of the data. CR completion and categorical variables will be analyzed using chi-square or Fisher’s exact test. Missing data will be replaced using the last observation carried forward or the mean value. In the case of more than 20% of dropouts, missing data in the intent-to-treat analysis will be replaced using multiple imputations. The intention-to-treat population will include all enrolled participants, and the per-protocol analysis will include patients who have completed the 3-month evaluation.

Changes in secondary outcomes over time for the CPET, KASI, EuroQol 5 dimensions, and patient health questionnaire will be analyzed using paired t-tests with comparisons from baseline. Analyses will be conducted for each of the intervention, control, CR completion, and non-completed groups. For non-normal distributions, the Wilcoxon signed-rank test will be used.

Statistical significance will be set at *P* < .05, and SPSS version 20 (IBM SPSS Statistics, New York, NY) will be used for the statistical analysis.

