## 1. Introduction

Cardiac rehabilitation (CR), which consists of supervised exercise programs, patient education, risk factor management, and stress control, is a customized intervention for patients with cardiovascular disease. CR has been most strongly indicated in patients with acute myocardial infarction (MI),^[1]^ and various studies have demonstrated its effect in reducing mortality, recurrence, and hospital readmissions while improving exercise capacity and quality of life.^[2–4]^

Although strong recommendations and benefits of CR have been emphasized in the literature, the actual participation rate in CR remains low worldwide. Among CR-eligible Medicare beneficiaries in the United States, only 24.4% participated in CR, of whom 26.9% completed the CR program.^[5]^ In Japan, CR participation rates were estimated to be as low as 3.8% to 7.6%.^[6]^ Globally, approximately 38.8% to 54.7% of countries have provided CR,^[6,7]^ but CR participation remains at approximately 30% to 40% worldwide.^[6,8]^

According to a global CR density report published in 2019, the CR density in South Korea was 22, ranking 27th out of 111 countries with CR programs.^[9]^ A national study reported CR density as approximately 10 AMI incidences/capacity/year, indicating that 10-fold more CR institutions are required for the yearly AMI incidence, with only 1.5% of acute myocardial infarction patients (960/64,982) participating in outpatient CR after discharge. Thus, despite CR coverage by the National Health Insurance, hospital-based CR remains underutilized in South Korea.^[10]^ Moreover, despite enrollment in outpatient CR starting at 47%, adherence to the program has decreased to 17% in regional cardiocerebrovascular centers in South Korea.^[11]^ Surveys of the medical staff in these centers indicated that time, distance, and transportation issues were relevant barriers to CR, followed by cost burdens. Additionally, a larger study questioning CR attenders compared with non-attenders indicated that patients identified logistical factors, such as distance, cost, and transportation problems, as major barriers to center-based CR.^[12]^ A systematic review analyzing studies of CR participation in the USA and Europe reported that lack of transportation or distance from CR facilities were important factors for low CR adherence.^[13]^

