Various intervention strategies have been implemented worldwide to increase participation and adherence to CR. A previous study by Gaalema et al^[14]^ reported a significant increase in CR participation with doubling of CR completion in patients with low socioeconomic status in the US by providing financial incentives to CR-eligible patients. Currently, there are insufficient studies exploring strategies to improve CR participation in South Korea and in Asia, in general.

We hypothesized that issues of transportation difficulties, cost burden, and time could be alleviated by providing financial incentives. Therefore, this study examines the efficacy of financial incentives as transportation aids for increasing CR participation and completion among acute MI patients in South Korea.

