### 2.4. Binding and allocation

The control and experimental groups will be randomized, with each group having a 1:1 assignment ratio. Group assignments will be determined using computer-based random number generators and will be known only by the research assistant after opening a sealed envelope containing a computer-generated sequence sheet.

The participants will know which group they belong to; however, the assessor will not be aware of each participant’s group, and the participants will be instructed not to inform the assessor. The person managing the data will not know the subject group until the analysis of the study is complete. If any participant is included in the study discontinuation criteria, the principal investigator will reveal the blinding and progress to standard treatment.

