**Figure 1. F1:**
[figure not shown]
Flowchart of the data collection.

During baseline assessment, basic demographic information (sex, age, body mass index, occupation, distance/time from home to the hospital, insurance type) and clinical information [cardiac arrest type, diagnosis, number of coronary artery stenosis/occlusion, intervention type/result, left ventricular ejection fraction (LVEF) (%), remaining coronary occlusion (%), lipid/glucose profile, echocardiogram findings, risk factor information (diabetes mellitus, hypertension, dyslipidemia, obesity), history of cardiocerebrovascular disease, laboratory results, body composition analysis and physical measurement, cardiopulmonary exercise testing (CPET) results, lifestyle risk factors (smoking, drinking, physical activity)] will be obtained through chart review. Additionally, basic information, patient-reported outcome measures (PROM), and clinical outcomes will be assessed.

At 3 months (assessment after completion of the exercise program), data will be collected on exercise therapy completion rate and the number of session participations.

At 3 and 6 months, body composition analysis, physical measurements, CPET results, PROM, and clinical outcomes will be assessed.

At 12 months, through chart review, echocardiography, laboratory test results, and medical information, if available, will be recorded, and body composition analysis and physical measurements, CPET results, PROM, and clinical outcomes will be assessed.

Patients who discontinue participation in the assessments during the study course will have values used in the analysis until the dropout period. All patients were sent an identical reminder text message informing the participants of the date, time, and location of the upcoming evaluation to promote patient retention and follow-up.

Table 1 presents the details of the data collection.

**Table 1 T1:** Schedule of enrollment, intervention, and assessments.

Timeline assessment item		① Consent	② Baseline	③ Exercise end point 3 months	④ 6 months	⑤ 12 months
Screening		√				
Enroll *		√				
Chart review †	Basic information		√			
	Occupation		√			
	Past history		√			
	Heart disease information		√			
	Cardiovascular imaging and detailed PCI Information		√			
	Echocardiography ‡		√			√
	Lab §		√			√
	Current medication		√			
	Cardiac rehabilitation information		√			
	KASI prior to the onset		√			
Intervention	Incentive		→			

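### The session-count test makes no use of baseline travel distance or time, which the protocol records and names as a main barrier; adjusting for it would be a cheap, modest gain, and the planned test is still valid

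*Protocol article*

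**What the plan says.** All references are to the protocol article.

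- **Analysis (section 2.11).** The session count, one of the primary outcomes in section 2.9.1, is handled as follows: "CR participation, defined as the number of sessions completed, will be analyzed as a continuous variable using the student" *t* test, with the Mann–Whitney *U* test as the alternative, depending on normality. No adjusted model appears for any outcome.
- **Baseline data (section 2.8.1, text below Figure 1).** The demographic items include "distance/time from home to the hospital".
- **Why that item matters (section 1).** Staff surveys found that "time, distance, and transportation issues were relevant barriers to CR, followed by cost burdens". In a larger study of attenders and non-attenders, "patients identified logistical factors, such as distance, cost, and transportation problems, as major barriers to center-based CR".
- **Hypothesis (section 1).** The trial expects that "issues of transportation difficulties, cost burden, and time could be alleviated by providing financial incentives".
- **Allocation (section 2.4).** "Group assignments will be determined using computer-based random number generators", in a 1:1 ratio. No stratification by distance is described. Section 2.5 plans 12 per group at each hospital, which at most balances site.

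**The concern.** Travel distance or time is the predictor of attendance that the protocol itself supports best. It is measured before treatment, and the analysis of attendance then leaves it out. The analysis plan may exist and is not shown, but section 2.11 is not silent on the method: it names two tests, and neither can adjust.

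Two things are at stake in a trial of 48 patients. If travel time explains part of the variation in sessions attended, adjustment would narrow the confidence interval for the arm difference. And if the arms happen to differ in travel time, part of the observed difference will reflect that, with no planned analysis to separate the two. An adjustment chosen after such an imbalance has been seen would be open to criticism, so the choice has value only if made in advance.

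**Working it through.** **Inputs from the protocol.** 24 per arm, 48 in total; planning rates 55.4% versus 15.4%; power 0.8 (section 2.5); significance at 0.05 (section 2.11), taken as two-sided.

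**Assumptions, not in the protocol.** r, the size of the within-arm correlation between travel time and sessions, is varied from 0 to 0.5. The calculations use normal data.

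**1. The plan's own figure.** For two proportions with pooled variance and no continuity correction, mean rate 0.354:

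n = [1.96 × √(2 × 0.354 × 0.646) + 0.842 × √(0.554 × 0.446 + 0.154 × 0.846)]² / 0.40² = (1.326 + 0.517)² / 0.16 ≈ 21.2, so 22 per group.

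The stated 22 reproduces. It rests on the completion rate, so nothing below alters the sample size.

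**2. Chance imbalance.** The standardised difference in mean travel time between arms has standard error √(2/24) = 0.289 SD and a 95% range of ±1.96 × 0.289 = ±0.57 SD. The chance of exceeding 0.5 SD is 2 × [1 − Φ(0.5/0.289)] = 2 × [1 − Φ(1.73)] = 8.3%.

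An imbalance of 0.5 SD shifts the unadjusted difference in sessions by 0.5 × r: 0.15, 0.20 and 0.25 SD for r = 0.3, 0.4 and 0.5. The standard error of that difference is itself 0.29 SD.

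**3. Validity.** In 10,000 simulated null trials at each of r = 0.3 and r = 0.5, type I error was 5.2% unadjusted in both cases, and 5.1% and 5.05% adjusted.

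**4. Precision, same slope in both arms.** The variance ratio of adjusted to unadjusted is (1 − r²) × [1 + 1/(48 − 4)] = (1 − r²) × 1.0227. Power is from the noncentral *t* distribution with 45 degrees of freedom, at 0.826 SD, the effect for which the unadjusted *t* test (46 degrees of freedom) has 80% power. Equivalent extra patients are 48 / variance ratio − 48.

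| r | Variance ratio | Adjusted power | Equivalent extra patients (total) |
|---|---|---|---|
| 0 | 1.02 | 79.1% | −1.1 |
| 0.2 | 0.98 | 80.7% | 0.9 |
| 0.3 | 0.93 | 82.7% | 3.6 |
| 0.4 | 0.86 | 85.6% | 7.9 |
| 0.5 | 0.77 | 89.2% | 14.6 |

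Break-even is where (1 − r²) × 1.0227 = 1, that is r = √(1 − 1/1.0227) ≈ 0.15.

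**5. Slopes that differ by arm.** If incentives relieve the travel barrier, distance should predict attendance less in the experimental arm. Simulated power at 0.826 SD, 20,000 trials for each row:

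| r in controls | r in experimental arm | Unadjusted | Adjusted |
|---|---|---|---|
| 0.4 | 0.2 | 80.2% | 82.9% |
| 0.4 | 0 | 79.9% | 80.6% |
| 0.3 | 0 | 80.3% | 80.2% |

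**6. A larger effect.** Suppose the planning rates are proportions reaching the 18-session threshold on a normal scale (an assumption). The implied difference is Φ⁻¹(0.554) − Φ⁻¹(0.154) = 0.136 + 1.019 ≈ 1.16 SD. Unadjusted power is then 97.5%. Adjusted power is 97.2, 97.7, 98.8 and 99.4% for r = 0, 0.2, 0.4 and 0.5.

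**The case against.** The strongest reply is that nothing here is wrong. A two-sample test is valid after 1:1 randomisation, and its standard error already allows for chance imbalance. A reader might infer from the missing covariate that the primary comparison is biased or its P value unreliable. The documents do not support that: type I error stays near 5%, and the plausible shift is smaller than the estimate's own standard error. This part of the objection stands in full.

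The benefit also rests on a correlation that the protocol does not give. Its evidence on barriers comes from staff surveys and from attenders compared with non-attenders. The trial enrols people who came for outpatient rehabilitation and agreed to take part (sections 2.3 and 2.3.1), so some of those deterred by distance are already absent and r may be weaker. This stands.

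The objection that bears most directly on this trial is that its own hypothesis works against the gain. If incentives remove the travel barrier, a common-slope model gains almost nothing (step 5). If the effect is as large as the planning rates suggest, there is little power left to add (step 6). Both stand. In addition, the comparison was made against a *t* test on normal data. It was not made against the Mann–Whitney test that may be used for a count bounded at 0 and 36.

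It can also be said that covariate adjustment is commonly left to the analysis plan. That does not carry here, because section 2.11 fixes tests that exclude it.

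**Conclusion.** The point holds as an optional improvement in efficiency and robustness, not as an error. The protocol collects a baseline variable that it regards as a main determinant of attendance, and fixes a primary analysis that cannot use it.

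The size is modest and conditional. With equal slopes and an effect of 0.826 SD, the gain is about 1, 3, 6 and 9 points of power at r = 0.2, 0.3, 0.4 and 0.5, equivalent to about 1 to 15 patients. Below r of about 0.15 there is no gain, and at r = 0 about 1 point is lost. If distance matters only in the control arm, the gain is under 1 point at r = 0.4 and nil at r = 0.3; at a 1.16 SD effect it is at most about 2 points. Protection against an awkward imbalance concerns an event with an 8.3% chance.

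A reader might also infer that the trial is underpowered for want of adjustment. That does not follow: the sample size was set on the completion rate, and the planning rates imply ample power for the session count under the assumption in step 6.

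**What to change.** Before unblinding, amend section 2.11 so that the session-count analysis is a linear regression of sessions on arm, with baseline travel time (or distance; name one) and hospital as covariates. Because the count is bounded at 0 to 36, specify robust standard errors or a permutation P value. Keep the unadjusted test as a sensitivity analysis and leave the completion test unchanged. If unblinded results have already been seen, report the adjusted model as a labelled sensitivity analysis instead.

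The cost is a change of analysis wording and a slightly less simple model, with no new data collection and no change to the sample size. The downside is one or two degrees of freedom, about 1 point of power if travel time does not predict attendance, and the need for complete travel-time data in all 48 participants.
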